#### 4.8.4 Allocation process

Clinicians will be randomized at the beginning of the study and, if necessary, when first treating an eligible patient. Clinician randomization will be stratified by study site and according to whether they are pediatric emergency clinicians or not. To maintain balance the randomization algorithm utilized will balance across the stratification factors dynamically as clinicians are enrolled.

Randomization will be assigned on a 1:1 basis across arms. Though we will not be able to blind parents and clinicians to use of the decision aid, we will blind the investigators and all nonclinical stakeholders to study arm.

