### **4.3.2 Patient Selection**

Each criterion must be addressed and documented in the patient’s case report form for eligibility assessment prior to randomization. No waivers or exemptions to any eligibility criteria are permitted.

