#### 4.4 Registration/Randomization Procedures

The flow and process of identifying eligible patients for enrollment in the study is depicted in **Appendix 2**.

Given the relatively limited number of pediatric clinicians at each site and the great degree of familiarity with the PECARN head CT decision rules across the specialty of pediatric emergency medicine, randomizing at the patient level is associated with a significant risk of contamination of the intervention. As such, we will randomize at the clinician level to limit contamination.

Informed consent will be obtained from clinicians at each site prior to enrollment of that clinician's parent/child dyad. After clinician consent is completed, the site study coordinator will contact the statistical team ([[name]/[name]](#)) with enrollment information via email. The statistician will centrally randomize the clinician and communicate that to the site principle investigator and study coordinator.

Informed consent will also be obtained from the parent/guardian of a child with minor head trauma. The parent must provide signed and dated consent for the use of their Protected Health Information (this may be incorporated into the informed consent document). Prior to registering a parent(s) to the study, all of the eligibility criteria on the eligibility checklist must have been met. **No waivers or exemptions to any eligibility criteria are permitted.** All eligibility criteria must be fully documented on the case report form and subsequently entered into the study database.

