## 4.7 Data collection

To assess the reach of the trial, study coordinators will record parents who are enrolled as well as those who were assessed for inclusion. The criteria for inclusion that the parents' child did not meet will be captured along with declines by the parent. This will allow us to measure participation and representativeness of the trial.

The enrolled parents' data will be collected via surveys prior to and after the encounter with the clinician where the disposition discussion took place. A study coordinator will collect data from the EMR for registration/randomization, and all subsequent data from time of initial visit for head trauma to 7 days after for follow-up to assess utilization and safety of the child of the enrolled parent(s). The types of resource utilization captured during the 7 day follow-up include: imaging data, outpatient visits and procedures, and inpatient hospitalizations (including admission and discharge dates, reason for admission, neurosurgical procedures, and discharge destination). The study coordinator will also obtain the PECARN risk estimate for each child whose parents provide consent. Parents will be provided a form on which to document this information at discharge from the ED or the hospital. This will allow for a more standardized collection of these data. We will also request that parents save all their healthcare bills that they receive during this 7-day period. The parent will be contacted 7 days after enrollment via phone (primary method of contact) for assessment of utilization and safety events. If the primary method of contact is not successful, the study coordinator will subsequently contact the parent(s) utilizing a secondary method

of contact that was obtained at time of consent (email, a secondary phone number, or mail) for completion of the 7-day assessment. Clinician's will be surveyed after each encounter with an enrolled parent.

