findings. We sought a meaningful measure for clinical decision-making which also accounted for the imperfect specificity of CT (i.e., false positive scans that might result in overnight admissions). Site investigators, blinded to ED data, will verify outcomes by medical record review. CT scans will be obtained at the ED clinician's discretion with helical CT scanners and interpreted by site faculty radiologists. A faculty radiologist, unaware of clinical data, will make definitive interpretations of inconclusive CT scans. Study coordinators will contact parents of children with minor head trauma starting at 7 days to ensure that no outcomes are missed. Medical records and imaging results will be obtained if a missed TBI is suggested at follow-up. If a ciTBI is identified, the patient's outcome will be classified accordingly. If we are unable to contact the patient's guardian by telephone or any secondary means of contact provided at the time of consent, we will review the medical record, emergency department/trauma process improvement records, and county morgue records, to ensure that no discharged patient is subsequently diagnosed with a ciTBI.

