### 6.3 Data management

All sites will be required to use the current version of all documents and forms and adhere to the study schedule. Study sites will transcribe subject source data into eCRFs using REDCap for registration and data collection. The REDCap system is a HIPAA compliant secure data entry system that allows for validated data entry, edit checks and logs of all data changes.

All subsequent data (parent eligibility criteria, EMR review, parent survey (pre and post encounter), clinician survey and the parent 7 day follow-up) will be captured in the REDCap system by the site study coordinator.. A copy of the signed consent, case report form assessing parent/child eligibility, where the clinician signs-off along with copies of all surveys (parent and clinician) will be uploaded into REDCap as a PDF or word document or sent into the coordinating center, if the site does not have the capability to scan and upload files, and transferred into electronic storage behind the Mayo Clinic firewall in the study folder where only approved staff has access. All paper copies provided to the coordinating center will be destroyed after the transfer has been completed.

The data within REDCap can be accessed by the statistical team at any time and downloaded into a statistical software package. The statistical team will review the data on a monthly basis to ensure data accuracy and completeness. All data, documents, and analysis findings will be housed within the Mayo Clinic system that is password protected and backed up on a nightly basis. The data will be stored within the secure system for seven years following completion of the study.

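### The stated blinding of investigators is contradicted by the allocation procedure, arm-blind ciTBI verification is not secured, and nearly all children are screened after the arm is known

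*Protocol*

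**What the plan says.** **Blinding.** Section 4.8.4 concedes that parents and clinicians cannot be blinded, then states that "we will blind the investigators and all nonclinical stakeholders to study arm".

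**Who is told the arm.** Section 4.4: "The statistician will centrally randomize the clinician and communicate that to the site principle investigator and study coordinator". Under section 4.5.1 the coordinator also picks the version of the aid and hands it to the clinician. Section 6.1 gives the tracking of wrong-intervention errors to the PI, the Co-PIs, the lead coordinator and the statistician.

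**Who verifies safety.** Section 4.7.3: "Site investigators, blinded to ED data, will verify outcomes by medical record review". Coordinators make the 7-day contact that is meant to catch missed events.

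**When eligibility is settled.** Section 4.3.2 requires each criterion to be documented "for eligibility assessment prior to randomization". Section 4.8.4: "Clinicians will be randomized at the beginning of the study and, if necessary, when first treating an eligible patient".

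**Who handles enrolment.** Section 4.7: "study coordinators will record parents who are enrolled as well as those who were assessed for inclusion". Section 6.3 describes a "case report form assessing parent/child eligibility, where the clinician signs-off".

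**The concern.** There are two separate issues, with different routes to bias.

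The first is outcome assessment. A reader of section 4.8.4 would conclude that no investigator knows which arm a child belongs to. Section 4.4 tells at least one investigator per site. If that person, or someone with access to the same list, verifies ciTBI, a judgement on whether an admission or procedure was due to TBI could be made with the arm in mind. Few events are expected, so each judgement carries weight.

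The second is recruitment. When clinicians are randomised before their patients are identified, allocation is not concealed at patient entry. Staff who know the arm decide whom to approach, judge eligibility and seek consent. The two patient groups can then differ before the aid is used, and randomising clinicians does not protect against that. Section 4.3.2 reads as if allocation were still unknown when eligibility is recorded, so the protocol claims a protection it does not have.

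**Working it through.** **Step 1. Blinding statement against allocation flow.**

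| Section | Role | Knows the arm? |
|---|---|---|
| 4.8.4 | Investigators | No (stated) |
| 4.4 | Site principal investigator | Yes, is sent the allocation |
| 4.4, 4.5.1 | Study coordinator | Yes, is sent it and supplies the aid |
| 6.1 | PI and Co-PIs | In effect yes: a wrong intervention is recognised only by comparing assigned with delivered |
| 4.8.4 | Treating clinician | Yes (conceded) |
| 4.7.3 | ciTBI verifiers | Blinded to ED data; arm not mentioned |

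A site principal investigator is an investigator, so the first two rows cannot both be true. Section 6.1 adds a second conflict. An analysis plan would not resolve either, because the protocol itself fixes who receives the allocation.

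**Step 2. What the verification sentence secures.** Withholding ED data may hide the treating clinician, and with it the arm. It does not help a verifier who already holds the allocation and can learn the clinician's name. Nothing in section 4.7.3 bars the site principal investigator from verifying, and the coordinator who first hears of a possible missed event knows the arm. Arm-blind verification is therefore possible but not secured.

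**Step 3. How many children could be screened before allocation.** Inputs: 950 children, about 75 clinicians and an average of 15 clinicians per site (section 4.8.3); seven sites (section 4.3.1). Take the case most favourable to the plan: every clinician is randomised only at a first eligible patient, and that child's eligibility is recorded first. At most one child per clinician then precedes allocation.

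- With 75 clinicians: 75 / 950 = 7.9%, so at least 92.1% come after.
- With 15 clinicians at each of seven sites: 7 × 15 = 105; 105 / 950 = 11.1%, so at least 88.9% come after.

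The plan's normal route is randomization at the start of the study, under which the share before allocation is nearer zero.

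**Step 4. Weight of one safety event.** Inputs: a ciTBI rate of 0.9% in both arms and a 2-point noninferiority margin (section 4.8.3).

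- Expected events: 0.009 × 950 = 8.55, about 8.6 in total and 4.3 per arm.
- Equal arms assumed: 950 / 2 = 475 children each.
- One event reclassified in one arm: 1 / 475 = 0.21 percentage points, and 0.21 / 2 is about a tenth of the margin.

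This shows how sensitive the comparison is to each classification. It does not predict that any event would be misclassified.

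**The case against.** The case on the other side is substantial.

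- **Verification.** A reader might infer that ciTBI is verified by people who know the arm. The documents do not say so. Verifiers are blinded to ED data, they are called site investigators and not site principal investigators, and most ciTBI components are hard events (death, long intubation, neurosurgery, an admission of at least two nights with TBI on CT). A radiologist unaware of clinical data reads inconclusive scans. All of this stands. What remains is that arm-blinding is neither stated nor ensured.
- **Cause of the enrolment exposure.** A reader might also infer that telling the site principal investigator is what unblinds eligibility. It is not. The clinician signs off and the coordinator screens, and both know the arm whatever the principal investigator is told. The exposure follows from clinician-level randomization, which section 4.4 justifies by the risk of contamination. That choice is not disputed here.
- **Every child.** This would be too strong, because a clinician randomised at a first eligible patient may have had that child assessed beforehand.
- **Existing protections.** The criteria are fixed, waivers are barred, all criteria must be met before registration, enrolment of ineligible subjects is monitored monthly, and section 4.8.1 adjusts for baseline differences. These limit the problem. They do not show whom staff chose not to approach, and adjustment covers only measured characteristics.
- **Screening log.** Section 4.7 gives participation and representativeness as its purpose but does not say these are its only use. Section 4.8.1 commits to CONSORT, and an analysis plan may contain a table by arm. Its absence from the protocol is therefore not counted as an error; the table is proposed only as part of the remedy.
- **Size of bias.** The documents contain no figure for differential enrolment or misclassification, so no estimate of actual bias in CT use or ciTBI can be given.

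**Conclusion.** The point holds in three parts. First, the blinding of investigators in section 4.8.4 is contradicted by section 4.4 and, in practice, by section 6.1. This rests on the text alone. Second, arm-blind verification of ciTBI is not secured; that unblinded verification will occur is not shown. Third, the timing in section 4.3.2 cannot hold for at least about 89% to 92% of children, given the planned 950 children and 75 to 105 clinicians, which leaves room for differential recruitment.

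The practical weight is moderate. The primary outcome is parent knowledge, and nothing here shows an effect on it. CT use and ciTBI are named outcomes, however, and the safety comparison rests on about 8.6 expected events at the planned 0.9% rate, each worth about a tenth of the margin if the arms are equal in size. As written, the trial would report protections that its procedures do not provide.

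**What to change.** 1. **Section 4.4:** send each allocation only to the coordinator who supplies the aid, with the unblinded statistician holding the list.
2. **Section 6.1:** assign the tracking of allocation errors to those two roles, so that the PI and Co-PIs need not know the arm.
3. **Section 4.7.3:** state that ciTBI verifiers have no access to the allocation list or to the treating clinician's identity.
4. **Section 4.8.4:** list exactly which roles are blinded and which are not.
5. **Section 4.3.2:** change the timing to prior to enrolment.
6. **Reporting:** give screened, eligible, declined and enrolled counts by clinician arm from the tracking log, adding the treating clinician to the log if that is not recorded.

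Items 1 to 4 deliver the blinding that can be delivered. Items 5 and 6 do not conceal the arm at enrolment, which this design cannot do, but they describe it correctly and make an imbalance in recruitment visible. Time-stamping the checklist would conceal nothing, since the coordinator already knows the arm.

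The cost is procedural wording, possibly one log field, and a split by arm in the flow diagram. No new staff are needed, and the design and sample size do not change. The downside is that site principal investigators no longer see the allocation list and must rely on the coordinator and statistician for allocation problems.

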#### 4.8.5 Healthcare Utilization

ED utilization will be estimated based on hospital billing data. Itemized hospital bills and UB-92 or UB-04 forms (summary billing statements) will be obtained for all patients for the 7-day period after the index visit. The UB-92 discharge form provides data on the patient encounters including demographic characteristics, discharge diagnoses, and discharge status (including death, but not its cause). For the economic analysis we will compare healthcare utilization descriptively and using multivariable models. For descriptive comparison of 7-day utilization we will utilize the Wilcoxon rank-sum test to account for the skewness of the outcome measures. We will estimate resource utilization using multivariable models, using the two-part or one-part generalized linear regression models. We will use a Park test to assess the appropriate distribution; use a two-part model for outcomes where more than 10 percent of the subjects have zero outcome measure. The covariates in the multivariable models will include factors that may not be accounted for in the randomization such as type of healthcare insurance and severity of illness. We will also analyze the results using a subset of patients who primarily receive their entire healthcare at the participating centers. We expect that this analysis will provide a sensitivity analysis of the overall trial results based on self-report.

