### 4.8 Statistical Analysis

#### 4.8.1 Analysis Plan

We will conduct the study according to the intention to treat principle, including all parent-children dyads in the arm to which they were randomized, regardless of whether they received the intervention assigned. We will adhere to the CONSORT guidelines to transparently report study results and ensure that sufficient information is included to allow for assessment of the study's internal and external validity.

We will compare outcomes between study arms using t-tests for continuous outcomes and  $\chi^2$  tests for dichotomous outcomes, adjusted for clustering by clinician and stratified by study site. If there are differences in baseline characteristics between the two study groups, these will be accounted for using hierarchical generalized logistic or linear regression models that include an indicator for study arm^28.

We will perform descriptive analyses to describe any potential heterogeneity of treatment effect (HTE) and facilitate synthesis of subgroup results in future meta-analyses. We will conduct descriptive HTE analyses by age, gender, parent race/ethnicity, GCS score, and level of parental education (collected in post-visit surveys). The outcomes assessed with HTE analyses will be the same as those assessed in the trial (e.g., patient-centered outcomes such as parental knowledge, engagement,

satisfaction and healthcare utilization). We will also conduct interaction testing to determine the interaction between the decision aid and each pre-specified patient characteristic.

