#### 4.8.3 Sample Size Estimation

Patient knowledge will be the primary outcome, as it was considered to be the most important endpoint by our patient representatives on the ED Patient Advisory Council. In order for the study findings to maximally impact practice and policy, however, we will need to be adequately powered to detect differences in the outcomes of interest to each of the stakeholders.

Accounting for a lost to follow-up rate of as high as 5% (there was 2% lost to follow-up in our pilot trial), approximately 75 clinicians (assuming an average of 15 clinicians/site) will enroll 950 patients. This will provide the following power to detect differences in each of the patient and stakeholder-important outcomes (using a 2-sided hypothesis test and an alpha of 0.05):

| Outcome (n = 950)                                                                                | Usual Care* | Decision Aid* | Difference | Power |
|--------------------------------------------------------------------------------------------------|-------------|---------------|------------|-------|
| Parent knowledge                                                                          | 44%         | 60%           | 16%        | >99%  |
| Parent engagement in the decision making process                                          | 7.0 (5.5)   | 27.0 (8.2)    | 20.0       | >99%  |
| Decisional conflict †                                                                     | 36 (19)     | 21 (21)       | 15         | >99%  |
| Trust in the physician                                                                    | 79 (20.0)   | 84 (20.0)     | 4.1        | 86%   |
| Parent satisfaction with the decision made (% agree or strongly agree they are satisfied) | 70.0 (26)   | 80 (26.0)     | 10.0       | >99%  |
| Safety (clinically-important traumatic brain injury) ‡                                    | 0.9%        | 0.9%          | 0%         | 82.5% |
| Proportion of children who undergo head CT §                                              | 49%         | 34%           | 15%        | 95%   |
| Healthcare utilization                                                                    | 8.3 (0.8)   | 6.8 (0.7)     | 1.5        | >99%  |

\*Estimates were determined from our completed randomized trial.

†Lower decision conflict scores indicate less conflict experienced by patients related to feeling uninformed.  

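### Section 4.8.5 does not carry the clinician-clustering adjustment of section 4.8.1 over to the Wilcoxon test and regression models for 7-day utilization

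*Protocol*

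**What the plan says.** Protocol section 4.4 makes the clinician the unit of randomisation: "As such, we will randomize at the clinician level to limit contamination". Section 4.8.4 stratifies that randomisation by site and by whether the clinician is a pediatric emergency clinician. Section 4.8.3 expects that "approximately 75 clinicians (assuming an average of 15 clinicians/site) will enroll 950 patients".

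Section 4.8.1 recognises the design. Its t-tests and chi-square tests are to be "adjusted for clustering by clinician and stratified by study site". Hierarchical logistic or linear models follow only if baseline characteristics differ between the arms.

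Section 4.8.5 sets separate methods for utilization. The first is a rank test: "For descriptive comparison of 7-day utilization we will utilize the Wilcoxon rank-sum test to account for the skewness of the outcome measures". The second is regression: "We will estimate resource utilization using multivariable models, using the two-part or one-part generalized linear regression models". The section also fixes a Park test for the distribution, a 10% threshold of zero values for using the two-part model, and covariates such as insurance type and severity of illness. It does not mention the clinician, robust standard errors, random effects or the randomisation strata, and it does not point back to 4.8.1.

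**The concern.** Children treated by the same clinician are not independent observations of the treatment effect, because they share the clinician and the allocation. Utilization as defined in section 4.7.3 includes hospital admission and CT, which depend in part on the treating clinician, so some correlation within clinician is likely. The standard rank-sum test and an ordinary generalised linear model take children as independent. Used here, they understate the standard error, so p-values are too small and intervals too narrow.

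This is more than a detail left open. Section 4.8.5 already fixes the test, the model family and a model-selection rule, and an analyst who followed it literally would leave the clustering out. Lower 7-day utilization is part of the hypothesis in section 1.0 and has its own row in the power table of section 4.8.3, so a false claim of reduced utilization would matter.

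**Working it through.** **Inputs from the protocol.** 950 children and about 75 clinicians, loss to follow-up up to 5%, and "using a 2-sided hypothesis test and an alpha of 0.05" (section 4.8.3). Equal allocation (section 4.8.4). Utilization 8.3 (0.8) versus 6.8 (0.7), difference 1.5, stated power above 99%.

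**Assumption.** The protocol gives no ICC or design effect. I take 0.01 to 0.10.

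**1. The plan's own figure.** With 475 per arm and SD 0.8, the standard error is 0.8 × √(2/475) = 0.052, and 1.5/0.052 is about 29. Power is effectively 100%, so the stated figure reproduces.

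**2. Cluster size.** m = 950/75 = 12.67. Section 4.8.3 reaches 75 at 15 clinicians per site, which is five sites, but section 4.3.1 lists seven. Seven sites at 15 give 105 clinicians and m = 950/105 = 9.05. Both are shown.

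**3. True error of an unadjusted test.** Design effect DE = 1 + (m − 1) × ICC. True two-sided error = 2 × [1 − Φ(1.96/√DE)]. At ICC 0.05 and m = 12.67, DE = 1 + 11.67 × 0.05 = 1.583 and 1.96/√1.583 = 1.558, so the error is 11.9%.

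| Assumed ICC | DE, m = 12.67 | True error | Simulated rank-sum error | DE, m = 9.05 | True error |
|---|---|---|---|---|---|
| 0.01 | 1.117 | 6.4% | 6.1% | 1.080 | 5.9% |
| 0.02 | 1.233 | 7.8% | 7.4% | 1.161 | 6.9% |
| 0.05 | 1.583 | 11.9% | 12.2% | 1.402 | 9.8% |
| 0.10 | 2.167 | 18.3% | 17.5% | 1.805 | 14.5% |

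The simulation applied the standard rank-sum test to lognormal data in 75 clusters of 12 or 13, with no treatment effect and 4,000 runs per ICC. At ICC 0 it gave 4.9%, as it should. Here the ICC is on the log scale.

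**4. Sensitivity.** After 5% loss, m = 12.03 and the error at ICC 0.05 is 11.6%. Unequal cluster sizes push it up: with DE = 1 + [(1 + CV²) × m − 1] × ICC and CV 0.5, DE at ICC 0.05 is 1.742 and the error about 14%.

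**5. Interval width.** An unadjusted interval is 1/√DE of the correct width: 0.95 at ICC 0.01, 0.79 at 0.05 and 0.68 at 0.10.

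**6. Does the power table show an ICC?** Only by back-calculation, and only if the whole gap between unadjusted and stated power is put down to clustering.

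- Head CT: 49% versus 34% gives 99.6% to 99.7% unadjusted (after and before 5% loss). The stated 95% implies DE 1.61 to 1.69, ICC about 0.055 to 0.06.
- Safety: 0.9% in both arms, margin 2%, one-sided 5%, gives about 94% to 95% unadjusted. The stated 82.5% implies DE 1.52 to 1.60, ICC about 0.05.
- Trust: the printed difference of 4.1 gives 86.8% to 88.5% unadjusted against a stated 86%, ICC under 0.01. The printed means, 79 and 84, differ by 5, and that difference would imply an ICC of about 0.05.

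**7. Power after adjustment.** Even at ICC 0.15, DE = 1 + 11.67 × 0.15 = 2.75. The effective size is 475/2.75, about 173 per arm, the standard error is 0.8 × √(2/173) = 0.086, and 1.5/0.086 is about 17. Power remains above 99% on the stated means and SDs.

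**The case against.** The best defence is that section 4.8.1 states a general intent. It speaks of comparing outcomes between arms with adjustment for clinician clustering, and utilization is one of the outcomes. Section 4.8.5 changes the test because of skewness and nowhere says that clustering is dropped. Its covariate list need not be exhaustive, a generalised linear model can carry cluster-robust errors, and a statistical analysis plan that is not shown may say so.

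Part of this stands. It would be wrong to infer that the protocol ignores clustering: section 4.8.1 shows that the team planned for it. But that clause is attached to t-tests and chi-square tests, its hierarchical models depend on baseline imbalance, and neither clearly covers the methods in 4.8.5.

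The rank-sum comparison is also labelled descriptive, and section 4.8.3 makes knowledge the primary outcome. Both lower the stakes. The label does not remove the problem, since a rank-sum test still yields a p-value, and the models carry no such label.

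A reader might also take 12% as the trial's error rate, on the ground that the power table points to an ICC of 0.05. The document does not support that. It states no ICC, the rows concern other outcomes (the safety row is a rare event under a one-sided noninferiority test), and the trust row points either way depending on which printed difference is used.

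**Conclusion.** The point holds, at moderate severity. Section 4.8.5 names methods that, run as written, do not respect the unit of randomisation, and it does not carry over the adjustment that section 4.8.1 requires for other tests. At any positive ICC the p-values are too small.

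The size is conditional. With 75 clinicians, the true error of a nominal 5% test is about 6% to 18% for an assumed ICC of 0.01 to 0.10. It is about 12% at 0.05, falling to about 10% there with 105 clinicians. These figures assume clusters of roughly equal size and no adjustment elsewhere in the analysis. The sample size is not called into question, and the primary outcome is untouched.

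**What to change.** State in section 4.8.5, and repeat in the statistical analysis plan, that:

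- the rank comparison allows for clustering by clinician, for example through a clustered rank-sum test or a permutation test that reassigns arms by clinician;
- the generalised linear models, including both parts of any two-part model, do the same, for example through cluster-robust standard errors, clinician random effects or a bootstrap that resamples clinicians;
- both analyses account for the randomisation strata, site and clinician type.

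The methods named are examples; what matters is that the adjustment is explicit. The cost is a few sentences, a little more programming and somewhat wider intervals (about 1.26 times as wide at an ICC of 0.05, √1.583). No change to the sample size is needed.
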